### Sample size

Using the PASS^13^ software a two sample *T*-test assuming equal variance in both groups was performed. The power was set at 0.80 and the significance level (α) at 0.05. A clinically meaningful difference between the postoperative stiff shoulder and non-postoperative stiff shoulder groups was defined as a mean difference of 2 pain units [37, 38] on a scale of 0–10 and the standard deviation of these means was estimated from a previous randomised controlled trial of postoperative shoulder pain to be 2.20 [39]. Assuming a low incidence of postoperative stiff shoulder of 10 % a sample size of 110 patients was determined. To allow for loss to follow up and postoperative exclusion a 20 % margin was included resulting in a required sample size of 132 participants.

### Analysis

The incidence of postoperative stiff shoulder will be determined using the treating surgeon’s clinical diagnosis informed by the Buchbinder criteria of restriction of motion of greater 30° in two or more planes of shoulder motion [40].

Patient demographics, baseline range of motion, pain, sleep and depression scores and outcome data will be presented for both outcome groups (postoperative stiff shoulder and no postoperative stiff shoulder).

The principal analysis will involve assessing whether or not a relationship exists between average pain scores and development of postoperative stiff shoulder. This will be by determining if there is a significant difference of the mean of the “average pain scores over the last 24 h” between both outcome groups at each recorded time point and over predetermined periods (first week postoperatively, first month postoperatively and from week four to ten postoperatively), adjusted for multiple comparisons using the Holm’s step down procedure [41].

Secondary analysis will assess depression and its relationship with PSS. A history of depression diagnosis as well as active depression at each time point, as assessed by the PHQ-9, will be assessed for an association with a diagnosis of PSS adjusted and not adjusted for baseline depression, and adjusted for multiple comparisons using the Holm’s step down procedure [41].

This study will also report the incidences of postoperative stiff shoulder after rotator cuff repair as well as subacromial decompression and excision of the distal clavicle not in association with rotator cuff repair.

Finally a series of range of motion criteria will be used to objectively determine a range of incidences of PSS in the same cohort (Table 1).

**Table 1 Tab1:** Criteria for diagnosing postoperative stiff shoulder

Criteria for diagnosing postoperative stiff shoulder
Clinician’s diagnosis
Range of motion thresholds in two planes, both required • Active elevation <100 degrees AND • Passive external rotation <30 degrees
Range of motion thresholds in two planes, at least one required • Active elevation <100 degrees OR • Passive external rotation <30 degrees
Restricted range of motion compared to contralateral side, at least two planes • Restriction of >30 degrees in TWO or more planes of movement
Restricted range of motion compared to contralateral side, at least three planes • Restriction of >30 degrees in THREE or more planes of movement

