In our review of the literature surrounding frozen shoulder and PSS we found an array of criteria for both frozen shoulder and PSS. Objective criteria consisted of range of motion thresholds [5, 8, 10, 11, 13, 15, 18, 19, 27], global range of motion deficits compared to normal values [16], and range of motion deficits compared to the contralateral side [6–9, 11, 12, 14, 15, 17, 19]. We believe that the pursuit of a consensus objective criteria for PSS, and frozen shoulder, is important and we aim to apply various criteria to our patient cohort to determine their sensitivity and specificity of each test for the treating surgeon’s clinical diagnosis. We hope that these results will stimulate discussion on this issue.

We also reviewed the literature for studies researching the risk factors of PSS post rotator cuff surgery and found a number of studies, whose results conflicted [5, 10, 13, 22, 26, 28]. There is a scarcity of literature analysing the incidence of PSS after subacromial decompression or excision of the distal clavicle not in association with rotator cuff repair.

There are a number of potential risk factors for frozen shoulder and PSS that have been studied. These include sociodemographic, medical and psychological factors. Age, a traditional risk factor for primary frozen shoulder has been found to be and not be associated the development of PSS, with both higher and lower age associated with PSS in separate studies [10, 13, 28]. Our review found multiple studies associating worker’s compensation claims with the development of PSS, however one study rebutted these findings [22, 26, 28].

Diabetes, another traditional risk factor for primary frozen shoulder, has been found to be and not be associated with the development of PSS [10, 22]. Multiple studies have shown that patients with PSS after rotator cuff surgery have higher pain levels at 12 weeks with one study also finding that higher pain levels at six weeks were associated [10, 22, 28]. No studies have assessed the relationship between pain levels in the first month postoperatively, the time when the initial inflammatory healing process begins, and the development of PSS.

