Anecdotally, psychological factors have long been believed to be associated with the development of frozen shoulder. Codman proposed a link between one’s constitution and the development of “frozen shoulder” when he first coined the term in 1934 and Coventry used the term “periarthritic personality” to describe these personal characteristics who “were a little run-down without anything particular the mater” [2, 29]. A number of authors have since looked at both personality traits and the mental health of patients with primary frozen shoulder [21, 25, 30–34]. The findings from these studies are conflicted and inconclusive and rely upon varying measures of personality and depression, although recent studies found that the mental health of patients with primary frozen shoulder was no different to that of the general population [32, 33]. No research has been done assessing a temporal relationship between depression and frozen shoulder’s related condition PSS. Given these historical views, depression’s known association with chronic pain and disability, and the described association of PSS with worker’s compensation claims we suggest that it is possible that patients who are depressed will be more likely to develop PSS [22, 26, 27].

The three aims of this study will be first to determine the incidence of postoperative stiff shoulder in patients of a single surgeon following arthroscopic subacromial decompression, and/or excision of the distal clavicle and/or rotator cuff repair rotator cuff repair; secondly, we will analyse the relationship between perioperative pain and depression, assessed by the Patient Health Questionnaire – 9, and the development of postoperative stiff shoulder, in patients following arthroscopic subacromial decompression, and/or excision of the distal clavicle and/or rotator cuff repair rotator cuff repair; thirdly, we will compare and contrast the incidences of postoperative stiff shoulder determined by different objective clinical criteria in the same patient cohort.

We hypothesize that patients who exhibit higher pain levels in the first month postoperatively will be more likely to develop PSS due to a more active postoperative inflammatory process. Secondly, we hypothesize that patients with depressed mood will be more likely to develop postoperative stiff shoulder. Thirdly, we hypothesize that different objective clinical criteria will determine different rates of postoperative stiff shoulder in the same patient cohort.

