Postoperatively participants will be clinically followed up at multiple time points. The operating surgeon will assess them at both their first and final postoperative consultations. The first consultation around the time of suture removal, and the second consultation three months after the operation. In addition the investigator will contact them by phone postoperatively on days two, five and seven and additionally at weeks four, seven and ten. At both postoperative surgeon clinical assessments the participants will asked to complete the PHQ-9. This will assess their mood over the previous two weeks. At their final postoperative consultation the range of motion of their treated shoulder will also be assessed. The senior surgeon will determine clinically whether or not the patient has ‘postoperative stiff shoulder’.

During each of the follow up phone calls, participants will be asked to complete the same pain questionnaires as preoperatively with the use of a verbal NRS and to detail the types of analgesia, dosage and any other treatment they have received in the last 24 h. The preoperative sleep assessment, using a verbal NRS, will be preformed postoperatively at these times. Participants will be asked what type and dosage of mediation (if any) they have taken to help them sleep in the last 24 h. Lastly patients will be asked to describe their mood over the past 24 h and also describe any events or stressors that may have impacted upon their pain, sleep or mood. This will be recorded on specifically designed form (see Additional file 3). Therefore each participant will have six phone assessments over the three months.

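### The rule of more than 30° restriction in two planes informs the surgeon's diagnosis and is then tested against it, so its sensitivity and specificity are biased upward by an unknown amount

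*Protocol article*

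**What the plan says.** Four places in the protocol article bear on this.

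- **Background, review of criteria.** The authors will apply various published criteria to the cohort to "determine their sensitivity and specificity of each test for the treating surgeon’s clinical diagnosis". The surgeon's diagnosis is thus the reference standard, and each criterion is an index test.
- **Analysis, first paragraph.** The incidence of postoperative stiff shoulder (PSS) will be "determined using the treating surgeon’s clinical diagnosis informed by the Buchbinder criteria", described there as "restriction of motion of greater 30° in two or more planes of shoulder motion". No comparator for the 30° is named in that sentence.
- **Analysis, Table 1.** Besides the clinician's diagnosis there are four objective criteria. Two use absolute thresholds for active elevation and passive external rotation (both required, or at least one required). Two use restriction relative to the contralateral side: "Restriction of >30 degrees in TWO or more planes of movement" and "Restriction of >30 degrees in THREE or more planes of movement".
- **Outcome assessment.** Range of motion is measured at the final consultation, where also "The senior surgeon will determine clinically whether or not the patient has" PSS. The article describes no blinding of the surgeon to the measurements and no second, independent diagnosis.

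The third hypothesis, at the end of the Background, is that "different objective clinical criteria will determine different rates of postoperative stiff shoulder in the same patient cohort".

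**The concern.** A sensitivity or specificity is interpretable when the reference diagnosis is reached without the test being assessed. Here one of the tests is an acknowledged input to the diagnosis. Whenever the surgeon lets the rule decide, rule and diagnosis agree automatically, and that agreement is counted as accuracy.

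The two threshold criteria for elevation and external rotation are not named as inputs to the diagnosis. They get no matching advantage, so a ranking of the four criteria is tilted towards the rule already in use. The Discussion hopes that the results will help in developing a consensus definition. A reader could take a high accuracy for the two-plane rule as evidence for that rule, when part of it only shows that the surgeon used it.

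A smaller point concerns the third hypothesis. Two pairs of criteria in Table 1 are nested, so a difference in rates within those pairs has only one possible direction.

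**Working it through.** **The plan's own figures.** The article states no sensitivity or specificity, so there is no accuracy figure to reproduce. Its sample size does reproduce: with 11 PSS and 99 non-PSS patients (10% of 110), a difference of 2, SD 2.20 and two-sided α of 0.05, the t-test has power 0.809. Nothing below depends on that calculation except the 10% incidence.

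**Inputs.** From the article: 10% incidence (Sample size) and a published range of 4.9% to 23.2% (Abstract). Assumed, because the article does not give them: the rule's true sensitivity and specificity against an independent clinical judgement, and the share *w* of patients in whom the surgeon follows the rule.

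**Model.** Let C be an independent clinical judgement and T the two-plane rule. The recorded diagnosis R equals T in a share *w* of patients and C in the rest. With incidence p, sensitivity Se and specificity Sp of T against C:

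- apparent sensitivity = [p·Se + w(1−p)(1−Sp)] / [p·Se + w(1−p)(1−Sp) + (1−w)p(1−Se)]
- apparent specificity = [(1−p)Sp + w·p(1−Se)] / [(1−p)Sp + w·p(1−Se) + (1−w)(1−p)(1−Sp)]

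In both, a positive *w* raises the agreeing cell and lowers the disagreeing one. Both measures therefore rise whenever the rule is imperfect.

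**Numbers at p = 0.10, Se = 0.70, Sp = 0.90.** The four cells of C by T are 0.07 (both positive), 0.03 (C only), 0.09 (T only) and 0.81 (neither). At w = 0.5:

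- sensitivity = (0.07 + 0.045) / (0.07 + 0.045 + 0.015) = 0.115 / 0.130 = 0.885
- specificity = (0.81 + 0.015) / (0.81 + 0.015 + 0.045) = 0.825 / 0.870 = 0.948

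| Share w following the rule | Apparent sensitivity | Apparent specificity |
|---|---|---|
| 0 | 0.70 | 0.90 |
| 0.25 | 0.80 | 0.92 |
| 0.50 | 0.89 | 0.95 |
| 0.75 | 0.95 | 0.97 |
| 1 | 1.00 | 1.00 |

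Averaging the two sensitivities (0.5 + 0.5 × 0.70 = 0.85) would be wrong here. Using the rule also changes who is diagnosed: 13.0% of patients at w = 0.5, not 10%.

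**Sensitivity to the assumptions, at w = 0.5.** With 0.70/0.90, apparent sensitivity is 0.92 at 4.9% incidence and 0.85 at 23.2%, with specificity about 0.95 in both. With 0.80/0.90 at 10% incidence, the result is 0.93/0.95.

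**Three-plane rule.** Everyone positive on three planes is positive on two. Where the surgeon follows the two-plane rule, a three-plane positive is always diagnosed, so its false positives shrink by the factor (1−w) and vanish at w = 1. Its sensitivity need not rise, because patients restricted in exactly two planes are then diagnosed and count as missed. The gain is mainly in specificity.

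**Third hypothesis.** Four objective criteria form six pairs. Two are nested: both thresholds within either threshold, and three planes within two. In these the rates are ordered in advance and are equal only if no patient falls between. The other four pairs, each a threshold criterion against a contralateral criterion, are not predetermined.

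**The case against.** The strongest reply is about scope. Sensitivity and specificity appear in one Background sentence only. The three stated aims, the Abstract, the Analysis section and the Discussion all speak of comparing incidences, and Table 1 lists the clinician's diagnosis as one criterion among five. This stands as a limit on importance: the affected output is subordinate. It does not remove the problem, because the Background sentence is a stated aim in the current text and names the reference standard. A later analysis plan could not undo the bias either, since it enters when the diagnosis is made.

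A second reply is that a diagnosis informed by a rule is not determined by it, and that the Analysis sentence names no comparator while Table 1 names the contralateral side. That also stands. The overlap is near-complete but not proven identical, and the direction of bias is clear while its size is not.

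A third reply is that any surgeon diagnosing stiffness will judge motion, since the definition adopted in the Background is itself a restriction of motion. This is right, and it limits what a change in the order of assessment can achieve.

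Three stronger readings are tempting and are not supported:

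- *The Outcome assessment and Analysis sections conflict.* They do not. A clinical determination is compatible with a clinical diagnosis informed by criteria; the Analysis section only gives more detail.
- *A confirmed third hypothesis would tell us nothing.* Four of the six pairs are not nested, and how far the rates differ is an empirical question even within the nested pairs.
- *The small number of cases is what hides the inflation.* Without an independent diagnosis it could not be detected at any sample size.

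**Conclusion.** The point holds in a limited form. As written, the plan assesses the two-plane rule against a diagnosis which that rule informs. Its sensitivity and specificity are therefore biased upward, the three-plane rule benefits mainly in specificity, and a comparison on accuracy with the elevation and external-rotation thresholds is not fair to the latter.

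Confidence is high for the direction and low for the size. The figures of 0.89/0.95 at half use and 1.00/1.00 at full use rest on an assumed true accuracy of 0.70/0.90, the article's 10% incidence, and a share of rule-following that the article does not state. A reader might infer that perfect accuracy is guaranteed; that would need the surgeon to follow the rule in every patient, which the article does not say. A reader might also infer that the pain comparison is compromised; this accuracy problem does not touch it. The planned comparison of incidences remains worthwhile, provided that the overlap is stated.

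**What to change.** - **Keep the outcome definition.** Removing the 30° rule from the diagnosis would change the outcome of the principal pain analysis for the sake of a subordinate aim.
- **Limit the accuracy analysis.** Do not report sensitivity and specificity of the two- and three-plane criteria against the surgeon's diagnosis, and do not rank them on accuracy against the elevation and external-rotation thresholds. Amend the Background sentence to match.
- **Report instead** the incidence under each criterion and the cross-classification between the four objective criteria. State plainly that the two-plane rule informs the clinician's diagnosis.
- **Third hypothesis.** State that differences within the two nested pairs can go only one way, describe their size, and base any inference on the four non-nested pairs.
- **Optional.** Have the surgeon record the yes/no diagnosis before the goniometer readings are taken. This reduces the dependence but does not remove it.

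The cost is a few sentences in the Background and Analysis sections and, if the option is taken, the order of two steps at the final visit. The downside is small: no accuracy estimate for two of the four objective criteria.

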**Discussion:**

This trial will add to clinical understanding of the postoperative stiff shoulder by providing further insight into the incidence of this condition following shoulder surgery and assessing whether perioperative pain and depression can be used as clinical predictors of postoperative stiff shoulder or markers for possible early intervention. This study will also allow the comparison of incidences determined by different objective criteria in the same cohort.

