## Method

### Design

This will be a prospective cohort study observing patients who will undergo surgery including arthroscopic subacromial decompressions and/or excision of the distal clavicle and/or rotator cuff repair.

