#### Outcome assessment

Baseline data collected from participant will include sex, age, dominant arm, shoulder side undergoing operation, history of diabetes mellitus and present treatment for diabetes mellitus, third party compensation status, history of depression, time since diagnosis of depression, whether participant is presently receiving treatment for depression and whether and type of previous surgery the participant has had on the shoulder undergoing operation (see Additional file 1).

Preoperatively participants will have range of motion assessed and be asked to complete a questionnaire encompassing pain, analgesia, sleep and mood (see Additional file 2). Range of motion of the shoulder will be assessed for each of the following planes of motion: active elevation, passive glenohumeral abduction with stabilisation of the scapula, passive external rotation in adduction and passive internal rotation in 90°, or maximal, abduction. This will be done using a goniometer. Average pain, worst pain at rest whilst seated with the arm at the side, worst pain with movement and worst pain at night over the last 24 h will be assessed using a visual numerical rating scale (NRS). The NRS pain scale is an 11 point scale where 0 = no pain and 10 = worst possible pain. Participants will be asked to detail the types of analgesia, dosage and treatment they have received in the last 24 h. Sleep will be assessed using a visual NRS sleep scale where 0 = worst possible sleep and 10 = best possible sleep. Participants will be asked what type and dosage of mediation (if any) they have taken to help them sleep in the last 24 h. Last, participants will be provided with a Patient Health Questionnaire – 9 (PHQ-9) that will assess their mood and depressive symptoms over the past two weeks and they will be classified as depressed or not depressed according to the DSM-IV criteria for a major depressive episode [35]. The PHQ-9 has a sensitivity of 98 % and specificity of 80 % for major depressive disorder when using the cutoff of 11 points or greater and allows for stratification of depression severity [35, 36].

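### The principal pain comparison names no adjustment for preoperative pain or operation type, so it cannot show that postoperative pain adds to either; an adjusted comparison should be reported beside it.

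*Protocol article*

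**What the plan says.** The Analysis section defines the main question: "The principal analysis will involve assessing whether or not a relationship exists between average pain scores and development of postoperative stiff shoulder". The answer is to come from the difference in mean 24-hour average pain between the two outcome groups, at each recorded time point and over three periods, "adjusted for multiple comparisons using the Holm’s step down procedure". No covariate is named. The Sample size section rests on a matching two-sample t-test.

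The next paragraph of the same section treats depression differently. History of depression and active depression "will be assessed for an association with a diagnosis of PSS adjusted and not adjusted for baseline depression".

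Both candidate covariates are available. Under Outcome assessment, the preoperative questionnaire covers "Average pain, worst pain at rest whilst seated with the arm at the side" and further pain items, on the same 0 to 10 scale as later. The Design section describes a cohort having "arthroscopic subacromial decompressions and/or excision of the distal clavicle and/or rotator cuff repair", and the operation performed is known for every patient. In the Analysis section, baseline pain is only tabulated by outcome group, and operation type is used only to report incidence with and without cuff repair.

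The aims use two kinds of language. The abstract's Discussion speaks of "assessing whether perioperative pain and depression can be used as clinical predictors of postoperative stiff shoulder", and the main Discussion wants pain as a marker for early intervention. The hypothesis at the end of the Background goes further and attributes the expected link to a more active inflammatory process after surgery.

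**The concern.** The groups are formed by outcome in an observational cohort, so nothing in the design balances them on preoperative pain or on the operation performed. Patients with more pain before surgery may have more pain after it. Cuff repair may differ from decompression or distal clavicle excision alone in both early pain and risk of stiffness. Either could produce a difference in postoperative pain between the groups even if postoperative pain carried no further information about PSS.

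The article itself decides on baseline adjustment for the secondary exposure and leaves it out for the principal one. If only the unadjusted result is reported, readers may take it as evidence that early postoperative pain independently predicts PSS or contributes to it, as the hypothesis proposes. The analysis as described could not bear that reading.

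**Working it through.** **1. The plan's own figure.** Inputs from the Sample size section: difference 2, SD 2.20, power 0.80, α 0.05 (two-sided assumed), PSS incidence 10% (ratio 1:9). For the smaller group, n = (1.960 + 0.842)² × 2.2² × (1 + 1/9) / 2² = 10.6, rounded up to 11. With 99 in the other group the total is 110, as stated, and 110 × 1.20 = 132. Power at 11 v 99 by the noncentral t is 0.81. The standard error of the difference is 2.2 × √(1/11 + 1/99) = 0.70 points.

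**2. Difference due to operation type.** All inputs are assumed: half the cohort has cuff repair, and PSS occurs in 15% with and 5% without it (10% overall).
- Cuff-repair share among PSS: 0.5 × 0.15 / 0.10 = 0.75.
- Cuff-repair share among no PSS: 0.5 × 0.85 / 0.90 = 0.47.
- If cuff repair is 1 to 2 points more painful, the group difference from this source is 0.28 × (1 to 2) = 0.28 to 0.56 points.

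**3. Difference due to preoperative pain.** Assumed: a 1-point preoperative difference between the groups and a slope of postoperative on preoperative pain of 0.3 to 0.5. The difference carried over is 1 × (0.3 to 0.5) = 0.3 to 0.5 points.

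**4. Range.** Either source alone starts at about 0.3. If the two do not overlap, the sum runs from 0.28 + 0.30 = 0.58 to 0.56 + 0.50 = 1.06. The overall range is about 0.3 to 1.1 points, up to about half of the 2-point target.

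**5. Chance of a significant result from the combined difference alone (11 v 99, SD 2.2).**

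| Difference | Single test at 0.05 | Test at 0.005 |
|---|---|---|
| 0.58 | 13% | 2% |
| 1.06 | 32% | 9% |

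The 0.005 level is Holm's first step for ten comparisons: six postoperative calls, the preoperative assessment and three periods. The figures are per test; the chance of at least one significant result is somewhat higher.

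**6. Power of an adjusted comparison.** The residual SD is 2.2 × √(1 − r²), with r the assumed correlation of pre- and postoperative pain (equal SDs, so slope = r). Tests are single, at 0.05, with 11 v 99.

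| r | Residual SD | Power if the adjusted difference is 2 | Adjusted difference if a 1-point baseline imbalance is part of the crude 2 | Power then |
|---|---|---|---|---|
| 0.3 | 2.10 | 0.84 | 2 − 0.3 = 1.7 | 0.71 |
| 0.5 | 1.91 | 0.91 | 2 − 0.5 = 1.5 | 0.69 |

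Overlap between PSS and the covariates lowers power a little further. With R² = 0.10 and the difference still 2, it is 0.81 at r = 0.3 and 0.87 at r = 0.5.

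**The case against.** Four points have force.

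- **A marker need not be adjusted.** If the question is whether patients in more pain more often become stiff, a crude association answers it, whatever lies behind the pain. A reader might infer that the unadjusted analysis fails the predictor aim altogether. The documents do not support that: the abstract and the Discussion ask for a predictor or marker. The gap concerns added value and mechanism only.
- **Preoperative pain is part of the exposure.** The second aim concerns perioperative pain, and pain is recorded before surgery, so a preoperative difference will be visible and on a natural reading is itself tested. Replacing the planned comparisons with an adjusted model would narrow the question. This stands, and it is why the adjusted result belongs beside the planned one.
- **The confounding inputs are all assumed.** The article gives no cuff-repair share, PSS rate by operation, pain difference by operation or pre/post correlation. Reporting incidence separately by operation does not show that the incidences differ. The upper end of the range also adds two sources that may overlap. So one can say that a difference could reflect baseline pain or operation type, but not that it would.
- **The article is silent on covariates and never says that the comparison is unadjusted.** An article may leave such detail to a fuller plan. Here the contrast with the depression paragraph makes the omission look like a choice, but that is an inference.

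It is also tempting to present adjustment as a sure gain in power. It is not: the gain requires the adjusted difference to remain at 2 points.

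**Conclusion.** The concern holds in a limited form. As described, the principal pain comparison is adjusted for multiplicity only, although preoperative pain and operation type are known and the depression analysis does get a baseline adjustment. The planned comparison is valid for a crude association. It cannot separate postoperative pain from what was already known by the end of surgery, and it cannot support the inflammatory explanation.

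The possible distortion of about 0.3 to 1.1 points rests wholly on assumed inputs. Even at its upper end, a false signal is not the likely result once Holm's procedure is applied. The study remains interpretable, so this is an improvement that should be made and not a fatal flaw.

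**What to change.** Keep the planned unadjusted comparisons at all planned time points and periods. Beside each postoperative one, report the PSS-group difference from a linear model of pain on PSS group, preoperative average pain and cuff repair (yes/no), following the pattern of the depression paragraph. State in the Analysis section that any claim that early postoperative pain independently predicts or contributes to PSS will rest on the adjusted result.

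Because pain is the dependent variable, the model uses about 110 patients for three terms. A logistic model of PSS with the same terms would have only about 11 events and is not needed for this point.

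The cost is a change of wording and slightly more analysis, with no new data. The adjusted difference may be smaller than 2 points, so its power may fall on either side of 0.80. The report should say that the sample size was set for the unadjusted comparison.
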